### Criteria for discontinuing or modifying allocated intervention (15b)

We do not plan to alter the allocated interventions based on participants’ responses to the intervention. However, we will encourage participants to engage with other interventions (outside the study) if they find that necessary. Participants may request a break or delay in their participation of up to four weeks at any point during the study.

### Strategies to improve adherence to intervention (15c)

Participants will receive automated reminder emails to encourage timely completion of tasks and questionnaires. Participants will have one week to complete each component with an automatic extension of up to one more week. As such, they will receive up to four reminder emails in total after the initial invitation to complete a part of the study, one reminder approximately every 3 to 4 days. If participants do not respond within 48 hours after the final reminder (sent on day 14), they will be automatically excluded from the study, but will still be compensated for time spent on the study so far.

For the e-couch modules, an automated reminder will be sent three days after the initial invitation. Since e-couch progress is managed by an external platform, we will not track participants’ activity on e-couch in real time. Therefore, each new email will remind participants to complete any outstanding modules from the previous week and encourage them to contact us if an extension is needed. To ensure participants access the correct modules, each email will include clear instructions and visual guides as to what to complete on that week. We will remind participants that following these instructions carefully is required to earn the $10 bonus. We will also instruct them to reach out to the research team if they encounter any issues or realize they have not followed the instructions correctly.

We will assess participants’ adherence to their assigned intervention condition after data collection is complete. Adherence will be defined based on the amount of engagement with the assigned interventions (time spent in e-couch modules and number of logins into the e-couch platform) and deviations from the assigned intervention protocol.

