**Figure 1 f1:**
[figure not shown]
Schematic diagram of study design and participant timeline.

At baseline, participants will complete QB1 (clinical symptom measures and a matrix reasoning task; approximately 35 minutes). They will then proceed to TB1 (four behavioral tasks; approximately 65 minutes) and after one day, to TB2 (two behavioral tasks; approximately 40 minutes). After completing TB2, participants will be randomly assigned to either the BA or CR group in a 1:1 ratio and can begin their five-week engagement with the e-couch program. Each module or submodule will require approximately up to 30–60 minutes per week, and participants will be encouraged to practice skills for a full week before progressing to the next module (see Section 15a, *Intervention and Comparator* for e-couch schedule).

While working through e-couch, participants will also complete additional assessments and behavioral tasks. Before starting e-couch week 2, they will complete QB2 (clinical symptom measures; approximately 7 minutes). Before e-couch week 4, they will complete TB3 (same questionnaires as in QB2 and four behavioral tasks; approximately 70 minutes). At the end of five weeks of e-couch, participants will complete QB3 (clinical symptom measures; approximately 30 minutes) to assess post-intervention symptoms.

Follow-up of symptoms will be assessed with questionnaires at 6, 18, and 42 weeks after study completion to assess immediate, mid-term, and long-term effects of the e-couch intervention. Each questionnaire will take approximately 7 minutes. For detailed description of the questionnaires and behavioral tasks, see **Figure 2** and Section 25, *Data collection method*.

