#### Study engagement

At any time, we may exclude participants from future portions of the study if they show a significant lack of response and/or involvement in the study components. For example, if a participant does not complete required study components in a timely manner after receiving email reminders, we will inform them that their participation in the study has been discontinued. In such cases, we will compensate participants for all portions they have already completed. If they had already received a token to access e-couch, the token will remain active, and they can continue using e-couch at their discretion.

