### Plans to promote participant retention and complete follow-up, including list of any outcome data to be collected for participants who discontinue or deviate from intervention protocols (25b)

We will encourage participants to complete the entire study, including all three follow-up questionnaires, by providing a $10 bonus upon completion of the final follow-up. Participants who withdraw before completing the study will also not receive performance bonuses earned from the behavioral tasks. Automated reminder emails will be sent to participants 7 and 14 days after the start of each follow-up. However, participants may complete each follow-up questionnaire up until the subsequent follow-up is sent out. For the final follow-up questionnaire, participants will have up to three weeks to complete it. For participants who choose to withdraw from the study after commencing it, we will document any reasons they provide by email and securely store this information in our database. When available, we will also record reasons for non-adherence (e.g., discontinuing due to burden or lack of interest) and non-retention (e.g., withdrawal or lost to follow-up). No additional data will be collected from participants who withdraw from the study.

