### Data management (26)

We developed software for an automated state machine to track each participant’s progress in the study and to manage study-related email communications. The system sends emails with invitations to specific parts of the study or the self-help tool, as well as reminder emails, based on completion of previous sections and time lags. The state machine runs on a secure server with encrypted file systems. Access is restricted to authorized study members working on this project and IT staff, all of whom must use two-factor authentication. The system records participants’ progress. Eligible participants identified in the screener will receive automatically a main study invitation, while ineligible participants will receive an email informing them that the study is not a good fit for them.

The state machine tracks how long a participant remains in each part of the study and logs every time point at which a participant starts or completes a task or questionnaire set. It also sends reminder emails to participants who do not complete task or questionnaire batches within the allotted time and automatically excludes participants who exceed the grace period, as detailed in section 15c, *Strategies to improve adherence to intervention*. The software also performs random assignment of participants to intervention and training/test groups and distributes e-couch tokens.

We note that the above steps occur automatically, without any involvement or influence from study team members. However, study team members may manually adjust a participant’ progress in the study if the participant requests to skip a task or ask for an extension. Such requests, as well as communication with participants beyond answers to clarification questions and providing payment information, will be documented in the database described below. Any complaints or events requiring IRB involvement will be documented and reported to the IRB through Princeton’s electronic IRB system (eRIA).

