### Who will be included in the analyses (27b)

For all analyses, we will include only participants who (a) met the assessed inclusion and exclusion criteria specified in Section 14a, *Eligibility criteria*, and (b) passed identity and attention checks at the beginning of the study. For predictive modeling and causal inference, the analytic sample will include participants who were randomized and had a baseline PHQ-9 total score greater than 4. This constitutes our intention-to-treat (ITT) sample.

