### How missing data will be handled (27c)

We anticipate a low proportion of missing data from self-report questionnaires and behavioral tasks from baseline as data collection is automated and participants can only advance after completing all components within a batch, i.e., such missing data will be missing completely at random (MCAR). Nevertheless, technical issues may occasionally result in missing data. We will impute missing data for questionnaires and task data using recommended imputation procedures such as Multivariate Imputation by Chained Equations (MICE, 90). Imputation will be applied for predictors and independent variables. As we assume that outcome data might be missing not at random (MNAR), we plan to not impute outcome data. However, we will examine all our assumptions about missingness mechanisms through sensitivity analyses and adjust our imputation decisions and analyses accordingly. During model development, imputation will be performed in a nested manner within the cross-validation framework such that imputation models are fit using only the training data within each fold, with no access to held-out folds. No auxiliary variables beyond the predictor set of the model under evaluation will be included in the imputation models (91). For models that make separate predictions per group, imputations will be conducted separately by intervention group (92). The finalized imputation strategy, including the predictor matrix, will be specified in the preregistered confirmatory analysis plan prior to evaluation on the held-out test dataset.

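### Randomised participants silent for about 16 days on QB2 or TB3 are excluded with no provision to collect their week-6 outcome, and suspected MNAR is given as the reason for not imputing it

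*Protocol article*

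**What the plan says.** Timing. The Participant Timeline (18) states: "After completing TB2, participants will be randomly assigned to either the BA or CR group in a 1:1 ratio". QB2 (about 7 minutes, before e-couch week 2), TB3 (about 70 minutes, before week 4) and QB3 (the post-intervention symptom batch) therefore all follow randomisation to arm.

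Exclusion. Section 15c gives the rule: "If participants do not respond within 48 hours after the final reminder (sent on day 14), they will be automatically excluded from the study". Data management (26) builds it into the state machine, which "automatically excludes participants who exceed the grace period" and sends invitations according to which earlier parts have been completed. The Study engagement paragraph of section 25 describes what exclusion means: "we may exclude participants from future portions of the study if they show a significant lack of response". The same paragraph leaves the e-couch token active. Section 25b, whose heading announces the outcome data to be collected from people who discontinue or deviate, lists none and adds: "No additional data will be collected from participants who withdraw from the study".

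Analysis. Section 27b takes participants who were randomised and had a baseline PHQ-9 above 4, with no condition on an observed outcome, and says: "This constitutes our intention-to-treat (ITT) sample". Section 27c says: "As we assume that outcome data might be missing not at random (MNAR), we plan to not impute outcome data".

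**The concern.** A participant can be randomised, go on using the assigned modules and never withdraw, yet stop being measured because one intermediate batch went unanswered. That missing outcome is produced by the trial's own procedure, and it falls on the less persistent participants.

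The reason in section 27c points the wrong way. Suspected MNAR is a reason to distrust standard imputation, but an analysis of observed outcomes alone is also generally biased under MNAR and rests on its own untestable assumption about those who are missing.

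Three things are at stake.
- The primary outcome is out-of-sample predictive accuracy. Training and test participants pass through the same filter, so good test performance says nothing about people who would have stopped answering.
- Participants learn their arm after QB2 (section 23). Loss at TB3 or later can therefore differ by arm and affect the personalised-advantage comparison of section 27a.
- Section 27d presents the ITT analysis as the one close to clinical use, so the gap between the defined and the analysed set matters for interpretation.

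**Working it through.** **1. Does the exclusion rule reach randomised participants before the outcome?** The order is QB1, TB1, TB2, randomisation to arm, QB2, TB3, QB3. The last reminder is on day 14 and exclusion follows 48 hours later: 14 + 2 = 16 days without response. Sections 15c and 26 contain no exemption after randomisation, so QB2 and TB3 are both points at which a randomised participant can be removed before QB3.

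**2. Is QB3 then withheld?** No sentence says so outright. It follows from three statements read together: exclusion is from later parts of the study (section 25), invitations depend on completing earlier parts (section 26), and no outcome collection is listed for those who discontinue (section 25b). No text points the other way. It does not apply to people who fail at QB3 itself, because they were sent it.

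**3. Defined set against analysed set.** Section 27b defines ITT by randomisation and baseline PHQ-9. Section 27c does not impute outcomes and names no other primary method, such as weighting or joint modelling, that would keep participants without an outcome. The analysed set is the ITT participants with an observed week-6 outcome.

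**4. Size.** Inputs from section 19: 1,500 recruited, 20% attrition, response prevalence 0.5. Training to test is 2:1.
- With an outcome: 1,500 × 0.80 = 1,200, that is 800 training and 400 test.
- Without an outcome: 1,500 × 0.20 = 300, that is 200 training and 100 test. This is an upper figure for loss after randomisation to arm, because section 19 does not say when the attrition occurs and the baseline batches come first.
- Illustration: section 21 expects over 700 per group. Assume 2 × 700 = 1,400 randomised and 1,200 measured. The loss is 200, and 200 / 1,400 = 14%. Only the part lost at QB2 or TB3 can be recovered by still sending QB3. The documents do not give that share.

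**5. What the observed data leave open.** Suppose 50% of those measured respond, the protocol's planning value. The response rate in everyone, from no missing participant responding to all of them responding, is:
- 300 of 1,500 missing: 0.5 × 0.80 = 40% to 40% + 20% = 60%.
- 200 of 1,400 missing: 600 / 1,400 = 43% to 800 / 1,400 = 57%.

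These are limits, not estimates. They concern the response rate, not predictive accuracy, on which the documents allow no calculation.

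**6. Context from the plan's own sample size.** The shrinkage criterion n = p / ((S − 1) ln(1 − R²/S)), with S = 0.9, R² = 0.05 and p = 5, gives 5 / (−0.1 × ln(1 − 0.05/0.9)) = 874.8, so 875, the protocol's figure. The 800 training outcomes in step 4 are below it, so avoidable outcome loss is not harmless.

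**The case against.** The strongest reply is that the rule is lenient and the analysis plan is open. Exclusion needs about 16 days of silence after up to four reminders. Extensions of up to a month (section 18) and breaks of up to four weeks (section 15b) are available on request. Section 27c promises to examine the missingness assumptions and to revise decisions accordingly. Section 27d adds delta adjustments and a comparison of included with excluded participants. The final missing-data procedure is left to the preregistration. All of this stands and softens the point. But extensions help mainly those who ask, the delta adjustments are framed as tests of imputations that the primary plan applies only to predictors, and no analysis recovers an outcome that was never requested.

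A reader might infer stronger things that the documents do not support:
- **That a merely late batch removes a participant.** It does not; see the 16 days and the extensions.
- **That the ITT analysis is a completers or per-protocol analysis.** Unfinished e-couch modules do not trigger automatic exclusion, people who skip the two aversive tasks are retained, and section 27d keeps per-protocol separate. The selection is on answering assessment batches.
- **That 200 training and 100 test outcomes are lost after randomisation and could be recovered.** This would put all attrition after randomisation and all of it at QB2 or TB3.
- **That the main harm is a biased mean or overall BA–CR contrast.** The protocol disclaims an overall comparison; its target is predictive accuracy and the personalised-advantage comparison.
- **That loss at QB2 differs by arm.** QB2 follows common week-1 content and precedes disclosure of the arm. Only later loss plausibly differs.

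Imputing outcomes in the test set would also be debatable, since predictions would then be validated partly against model-generated values.

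**Conclusion.** The point holds in this form. The protocol stops measuring some randomised participants who have not withdrawn, and it gives a reason for leaving their outcomes out that does not support doing so. The set analysed is smaller than the ITT set it defines, and the held-out test cannot show the effect.

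The loss after randomisation is at most 300 of 1,500 at the planned attrition, and about 200 (14%) if 1,400 are randomised and 1,200 measured, which is an assumption. An unknown part of that occurs at QB2 or TB3. The conclusion that QB3 is not sent is inferred from sections 15c, 25 and 26 rather than stated. The direction and size of any effect on accuracy, or on the personalised-advantage comparison, cannot be derived from the documents.

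**What to change.** **Data collection (state machine; sections 15c, 25 and 26).** Record an unanswered QB2 or TB3 as missed, and still send QB3 (at least PHQ-9 and QIDS) and all follow-ups unless the participant withdraws.

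**Analysis (sections 27b to 27d).**
- Drop suspected MNAR as the reason for omitting outcomes.
- Describe the observed-outcome analysis as ITT participants with an observed week-6 outcome.
- Add a sensitivity analysis for missing outcomes. One option is inverse-probability weighting using baseline and whatever QB2 or TB3 symptom scores exist, together with an extension of the section 27d delta adjustment to outcomes. Weighting avoids scoring test-set predictions against imputed values.
- Report numbers lost by batch and by arm, so that the reachable share is known.

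**Cost.** A rule change in the automated mailer, IRB notification and small extra payments. At the protocol's 15 USD an hour, a 30-minute QB3 is 7.50 USD, so 200 × 7.50 = 1,500 USD even if all 200 in the illustration were reached and answered, plus the ordinary follow-up payments. The analysis changes can go into the test-set preregistration, which the protocol treats as still to come, and so also cover participants already lost.

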### Concomitant care that is permitted or prohibited during the trial (15d)

Participants may continue any other care they were receiving or engage in additional care, that is, “usual care” will be permitted in both groups. At the end of the main study (week 6) and during follow-up visits, we will ask participants to report any care they received using the Psychiatric Treatment Questionnaire (see **Supplement *Study-specific measures***).

### Outcomes (16)

Our primary outcome is NOT a change in a specific symptom score or the superiority of one intervention over another. Instead, we aim to predict end-of-main-study (week 6) depression symptoms – both overall, and differentially for the BA and CR groups – in a held-out test dataset. Thus, our primary outcome is the out-of-sample predictive accuracy of improvement of depression symptoms using potential moderators. The prediction models will incorporate self-reported questionnaire data (clinical and demographic information) and computationally derived learning and decision-making variables from the behavioral tasks. Thus, our specific outcome depends on the exact target question and is tightly intertwined with the employed analysis approach. For more details on the specifications of the analysis approach and outcomes, see Section 27, *Statistical methods*. Also note that our primary outcome, as well as all trial estimands, will be precisely defined in the preregistration of the analyses of our untouched test dataset (and corresponding code). The separation of our data into a training and test dataset from the beginning of the study makes the specific definition of primary and secondary outcomes redundant at this stage.

### Harms (17)

The study will be conducted entirely online. Thus, we will only be informed about any possible harm that occurred if participants contact us via email or phone. Hence, harms will be assessed unsystematically. The PI, who is blinded to the allocation group, will decide whether the reported harm exceeds the threshold to be considered an adverse event. In such cases, we will report the event to the IRB and follow their guidelines regarding the adverse event.

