### Ancillary and post-trial care (34)

Participation in the study involves minimal foreseeable risk, primarily related to the emotional responses that may be invoked by questions in the self-report questionnaires, or images and sounds presented during the tasks. Some of the visual stimuli involve very disturbing and graphic contents (e.g., an image of a person getting hit by a car, or an image of mummified bodies), which participants may find troubling. In addition, this study involves being exposed to three kinds of screams that may be startling and unpleasant. The study also includes a variety of psychiatric symptom questionnaires. These do not permit formal diagnosis of clinical conditions, however, the questionnaires do assess symptoms associated with psychiatric disorders such as depression and anxiety, including one question that touches on suicidality. The sensitivity of the material might, in principle, be troubling to participants or might bring their attention to issues already of concern. Hence, throughout the study, and especially at each timepoint in which participants are asked to provide mental health information or engage with aversive stimuli, we will provide a participants with a “Mental Health Resource Page” (see **Supplement *Mental health resources page***) and encourage them to seek further help if needed. This is to ensure that if a participant experiences significant distress due to the questions or the task, they have resources for support at their fingertips. We opted to ask about suicidality given that empirical work suggests there is no evidence that asking about suicidal ideation increases the risk of suicide (95), and do not exclude participants based on suicidal ideation to not discriminate against them in a study that can help with such symptoms. Indeed, providing details of access to care might reduce ideation and promote treatment seeking.

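### Section 17 is overbroad in saying harm is known only through participant contact: symptom worsening is measured on a schedule and could be tabulated by arm

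*Protocol article*

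**What the plan says.** Protocol article, section 17 (Harms), starts from the study being entirely online and states: "Thus, we will only be informed about any possible harm that occurred if participants contact us via email or phone". It then concludes: "Hence, harms will be assessed unsystematically". The PI, blinded to allocation, decides whether a reported harm counts as an adverse event and, if so, it goes to the IRB.

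Section 18 (Participant Timeline) sets out the symptom measurements:

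- Baseline: "At baseline, participants will complete QB1 (clinical symptom measures and a matrix reasoning task; approximately 35 minutes".
- After the first e-couch week: "Before starting e-couch week 2, they will complete QB2 (clinical symptom measures; approximately 7 minutes".
- Mid-intervention: "Before e-couch week 4, they will complete TB3 (same questionnaires as in QB2 and four behavioral tasks; approximately 70 minutes".
- Post-intervention: "participants will complete QB3 (clinical symptom measures; approximately 30 minutes) to assess post-intervention symptoms".
- Afterwards: "Follow-up of symptoms will be assessed with questionnaires at 6, 18, and 42 weeks after study completion".

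Section 34 describes the symptom questionnaires as "including one question that touches on suicidality". Section 25 lists a Return of symptoms questionnaire with a response option for being worse than at the start of the study. Section 15d collects care received at week 6 and at follow-up. Section 26 stores the assigned arm for each participant. The article neither defines deterioration nor plans to report worsening by arm. Section 12 states that safety is not an aim.

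**The concern.** Section 17 moves in two steps, from online conduct to contact as the sole source of information, and from there to unsystematic harms. The first step does not fit the data collection plan. In a depression trial, getting worse is a possible harm, and the automated questionnaires record it on a schedule.

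Two things are at stake. Spontaneous reports carry no usable denominator: the absence of a message may mean that nothing happened or that nobody wrote, so a harms statement resting on them alone says little. And the trial asks who benefits from which intervention. How many participants ended worse than they began in each arm is a natural descriptive companion to that question, and the data for it will already be held.

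**Working it through.** Section 17 gives no figure to reproduce. The check is a comparison of sections, followed by an illustration of precision.

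**1. Is contact the only source?** After baseline (QB1) there are six scheduled symptom assessments: QB2, TB3, QB3 and the follow-ups at 6, 18 and 42 weeks. None needs participant-initiated contact; section 25 says all data are collected automatically. For symptom worsening, *only* is therefore not accurate. For distress during the aversive tasks, or events that no questionnaire asks about, it is.

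**2. Which assessments carry a by-arm contrast?**

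| Assessment | What has happened by then | Use for a by-arm contrast |
|---|---|---|
| QB2 | Both arms have had only the shared week 1 psychoeducation (15a); participants still blinded (24) | None |
| TB3 | Arm-specific modules of weeks 2 and 3 | Yes |
| QB3 | All arm-specific modules; other modules not yet opened (15a, 34) | Yes |
| Follow-ups at 6, 18, 42 weeks | Participants may use the other arm's modules (15a) | Not attributable to arm |

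Five of the six assessments follow the start of arm-specific content, but only TB3 and QB3 also precede cross-arm access.

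**3. Precision at week 6.** Inputs: 1,500 recruited and about 20% attrition (section 19); about 95% with PHQ-9 above 4 (section 14a); 1:1 allocation. Number per arm:

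1,500 × 0.95 × 0.80 / 2 = 570.

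The documents give no worsening rate, so a range r is assumed, equal in both arms. The 95% half-width for the difference is 1.96 × √(2 × r × (1 − r) / 570).

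| Assumed r | Expected number per arm (570 × r) | Half-width of the difference (percentage points) |
|---|---|---|
| 3% | 17.1 | 2.0 |
| 5% | 28.5 | 2.5 |
| 10% | 57.0 | 3.5 |
| 15% | 85.5 | 4.1 |

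At r = 5%, the half-width for a single arm is 1.96 × √(0.05 × 0.95 / 570) = 1.8 points.

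**4. What the intervals leave out.** Before attrition there would be 1,500 × 0.95 / 2 = 712.5 per arm. If all attrition came after allocation, 712.5 − 570 = 142.5 per arm would be unassessed, more than the expected number worsening at any rate in the table. Non-responders are excluded automatically (15c), nothing is collected after withdrawal (25b), and section 27c allows that outcomes may be missing not at random. The half-widths describe sampling error only.

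**The case against.** The best defence is that section 17 describes how an event reaches the team and is judged while the study runs. A stored score is not a notification, and section 27 says held-out test data are not observed by a human during the study, so for about a third of participants scores could not alert anyone. Read that way, the sentence is largely accurate. This stands, and contact should remain the route for event notification.

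It is also fair that a worse score is not in itself a harm, that the limitation is disclosed, that safety is not an aim, that risk is judged minimal, and that outcome definitions are deferred to the preregistration (section 16). Participants who worsen are not lost from the main analysis either, since week-6 depression is the prediction target, modelled separately by arm for the differential predictions. These points keep the matter small. They do not rescue the inference as worded, because section 17 speaks of any possible harm and derives unsystematic assessment from online conduct.

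A reader might go further and infer that harms as a whole are measured systematically, or that a by-arm table at every time point would show which intervention does more harm. The documents support neither. Some harms do depend on contact; QB2 precedes arm-specific content; follow-ups are open to cross-arm use; and dropout may distort the contrast. Nor does the text say at which time points the suicidality question is asked. The figure listing the batches is not shown here, so its repetition cannot be assumed.

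**Conclusion.** The point holds in a limited form. Section 17 is overbroad, not wrong throughout: one form of possible harm, symptom worsening, is measured on a schedule in participants still active, and the stated approach makes no use of it for harms reporting.

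The precision shown above, about 2 to 4 points for the week-6 difference, rests on the planned recruitment, attrition equal in both arms, the 95% share and assumed worsening rates. It applies to week 6 and not to every time point. The table would be descriptive: it would not separate intervention effects from natural course, and selective dropout may leave worsening under-counted, possibly unequally by arm. Severity is low; the primary prediction analyses are unaffected.

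**What to change.** 1. Reword section 17 to say that spontaneous contact covers events outside the questionnaires, and that symptom worsening will be summarised from the scheduled assessments.
2. Add a descriptive table by arm at TB3 and QB3. Give the number and percentage whose depression score worsened from baseline by an amount fixed in the preregistration. Where the suicidality item was collected at both times, also give the number scoring higher than at baseline.
3. Show alongside, per arm, the numbers randomised, assessed, and missing or excluded.
4. Report worsening at the three follow-ups without attributing differences to arm.
5. Report training-set figures earlier if wished; release test-set figures only after that set is unlocked.
6. State in a footnote that worsening includes natural course, that there is no untreated arm, and that dropout may bias the counts.

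The cost is a short rewording, one threshold in the preregistration and one table, with no new data collection. The main downside is over-reading, which items 3, 4 and 6 are meant to limit.
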